#### Plans for collection, laboratory evaluation, and storage of biological specimens for genetic or molecular analysis in this trial/future use {33}

These are not applicable, no samples collected.

### Statistical methods

#### Statistical methods for primary and secondary outcomes {20a}

An excel database will take downloadable data from the tablet computer used for the cognitive evaluation. The pharmacist will maintain randomisation codes, and the research team will maintain basic demographics information. Analyses will be performed in the SPSS and R statistical packages [95]. Differences in our primary outcome of processing speed between treatment and control arms at 12 weeks will be assessed adjusting for the stratification factor (i.e. hydroxyurea) and baseline measures as appropriate. Secondary outcomes will be similarly compared using linear, logistic, or Poisson regression models applicable to the outcome type (numeric, binary, or count). The primary analyses will be intention-to-treat on those patients who consented to randomisation. We will use bias-corrected and accelerated 95% confidence intervals (CI) for all analyses as they adjust for possible bias and determine significance at an alpha level of *p* < .05 two-tailed.

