#### Outcomes {12}

The research team will collect demographic, education, and health information from medical records, and participants’ caregivers will complete questionnaires. Caregivers will complete three questionnaires related to sleep as they capture related but distinct information about sleep habits, sleep-disordered breathing, and general sleepiness. We will obtain cognitive data (processing speed, executive function) from performance on tasks administered via a tablet computer. We will calculate both raw and norm-calculated standard scores (Mean = 100; SD = 15) in cognitive data analyses. We will calculate the Processing Speed Index (PSI) from the Wechsler subtests administered using scores from two subtests (substituting the third test if necessary). Executive function scores will be calculated from the NIH Toolbox® for Assessment of Neurological and Behavioral Function (NIH Toolbox®) Cognition Module [73] to obtain a composite that has been used in previous research [20]. We will obtain laboratory values (e.g. complete blood count, haemoglobin analysis, HbS%, HbF%) collected as standard care from medical records. When possible, we will collect data regarding brain function using MRI techniques and data regarding sleep from home oximetry (see Table 2 for the trial assessment schedule).

The primary and secondary outcomes have clinical relevance as they represent many of the significant co-morbidities (e.g. slowed processing speed, reduced white matter integrity, respiratory symptoms, sleep disturbances, pain, and low quality of life) experienced by paediatric patients with SCA [22, 45, 74–76]. The cognitive tests and questionnaires have been validated in numerous previous studies, often with a paediatric SCA population. The primary and secondary outcomes’ potential risks are minimal and only include those associated with routine cognitive testing and MRI scans. Testing procedures may induce boredom, fatigue, emotional discomfort, anxiety, or frustration. There is a rare risk that we may identify a previously undiagnosed learning disorder during the study. If that is the case, we will notify the caregiver and refer them to a proper specialist. We will screen participants for contraindications to MRI. If contraindications are found, the participant will not undergo MRI but can complete other study procedures if willing.

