#### Sample size {14}

Our sample will include 200 patients with SCA (i.e. HbSS or HbSβ^0^ thalassaemia) with some evidence of sleep-disordered breathing (e.g. snoring and overnight oximetry outside the normal range) aged between 3 and 7.99 years (see Table 1 for a full description of eligibility criteria). The primary outcome for this study is processing speed. We chose this outcome based on our previous research in SDB alone [77] and current preliminary findings in children with SCA and sleep-disordered breathing [46, 78]. Scores on the tests of processing speed are normally distributed (Mean = 100; SD = 15). Our study of preschool children with SCA showed slightly greater variability (SD = 16), and so this value was used in the sample size calculations to give a more conservative estimate. Statistical analyses determined that two groups of 100, one on montelukast and one on placebo, will give 90% power to detect a standardised difference of 0.5 at the 2.5% significance level, which equates to 8 points assuming an SD of 16. This difference is of clinical significance.

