### Assignment of interventions: allocation

#### Sequence generation {16a}

Each participant will either be receiving hydroxyurea or standard care, which will form a 2-category stratification variable. A computer programme (SIMIN package) will generate a stratified blocked random allocation sequence with randomly assigned block sizes (4, 6, 8, or) to ensure suitable allocation concealment. There will be an equal allocation distribution between montelukast (treatment) and placebo (control).

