### Primary outcome

#### Processing speed

The Cancellation, Symbol Search, and Coding subtests from the Wechsler Preschool & Primary Scale of Intelligence Fourth Edition (WPPSI-IV) [81] and the Wechsler Intelligence Scale for Children Fifth Edition (WISC-V) [82] will be used to calculate our primary endpoint of processing speed. We will give all three processing speed Wechsler subtests to obtain a two subtest Processing Speed Index. We will use this testing strategy to ensure that we have two usable processing speed scores from all patients. We will choose the most developmentally appropriate test for patients. All tests will be administered using Q-interactive [83] on a tablet computer and following published guidelines for remote assessment (if testing in a separate room is necessary). Cancellation requires the child to scan a structured arrangement of coloured shapes and mark target shapes within a specified time limit. For the WPPSI-IV, processing speed subtests include Bug Search and Animal Coding. Bug Search requires the child to match visual stimuli. Animal Coding is a speeded paired-associates subtest in which the child marks shapes that correspond to animals. For the WISC-V, we will administer the analogous Symbol Search and Coding subtests.

For our second primary processing speed endpoint, we will administer the Pattern Comparison Test, a subtest in the Cognition Module of the NIH Toolbox®. The cognition module includes automated scoring; however, the assessor presents task instructions, monitors compliance, and ensures valid results. All instructions will be presented visually on the tablet screen using the iPad app with instructions spoken orally by the assessor. Participants use their index fingers to identify whether two side-by-side pictures shown on the tablet screen are the same (press the ‘Yes’ button) or are not (press the ‘No’ button) the same. Participants have 90 s to respond to as many pictures as possible. The number of correct responses completed will be scored, up to a maximum of 130.

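### The sample size is planned at a 2.5% level, but the analysis section judges both primary endpoints at two-sided 5%, so the primary decision level contradicts itself

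*Protocol article*

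**What the plan says.** Four statements in the protocol article bear on the primary decision.

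- **Endpoints.** Under Processing speed, three Wechsler subtests "will be used to calculate our primary endpoint of processing speed" through a two-subtest index. The same section continues: "For our second primary processing speed endpoint, we will administer the Pattern Comparison Test". These are separate instruments with separate scores, and no composite of them is defined.
- **Planning level.** Sample size {14} says that 100 children per arm "will give 90% power to detect a standardised difference of 0.5 at the 2.5% significance level". It translates that effect into a gap of 8 points, taking the SD as 16. It does not say whether 2.5% is one-sided or two-sided, or why 2.5% was chosen.
- **Decision level.** Statistical methods {20a} will "determine significance at an alpha level of *p* < .05 two-tailed" and applies 95% bias-corrected and accelerated intervals to all analyses. The primaries are not exempted.
- **Claim.** The primary hypothesis is a single statement that processing speed improves on montelukast. The article gives no alpha split, no order of testing and no requirement that both endpoints succeed.

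**The concern.** The level that fixed the sample size and the level that will decide the result should be the same, and here they appear to differ by a factor of two. With two primary endpoints and one general hypothesis, a significant result on either test could be presented as confirming the hypothesis. If each test is run at two-sided 5%, the overall error rate exceeds 5%, even though the trial appears to have been sized to avoid this. The reported 95% intervals would also not correspond to a 2.5% decision. The practical danger is a primary p-value between 0.025 and 0.05, where the choice of level decides whether the trial is reported as positive.

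**Working it through.** **Inputs.** Difference 8 points, SD 16, so d = 8/16 = 0.5; power 90%; 100 per arm; level 2.5% (all from Sample size {14}). Analysis level two-sided 5% (from {20a}). The correlation between the two test statistics is not given, so it is varied as an assumption.

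**Step 1: which level reproduces 100 per arm?**
n per arm = 2(z_alpha + z_power)² / d² = 8(z_alpha + 1.2816)².

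| Reading of the level | z_alpha | n per arm | Power at 100 per arm |
|---|---|---|---|
| Two-sided 2.5% | 2.2414 | 8 × 3.5230² = 99.3 | 90.2% |
| One-sided 2.5%, or two-sided 5% | 1.9600 | 8 × 3.2415² = 84.1 | 94.2% |
| One-sided 5% | 1.6449 | 8 × 2.9264² = 68.5 | 97.1% |

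Power is Φ(d√(n/2) − z_alpha) with 0.5 × √50 = 3.5355; for example, Φ(3.5355 − 2.2414) = Φ(1.2941) = 90.2%. A t-test calculation agrees: at two-sided 2.5% it needs 100.6 per arm and gives 89.8% power at 100; at two-sided 5% it needs 85.0.

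The plan's figure reproduces, but only at two-sided 2.5%. This rules out the reading that would reconcile the two sections, a one-sided 2.5% equal to a two-sided 5%.

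**Step 2: error rate if either endpoint can carry the claim.**
Independent tests at two-sided 5%: 1 − 0.95² = 9.75%. Counting only results that favour montelukast: 1 − 0.975² = 4.94%, against 2.5% for a single test. Correlated cases use the bivariate normal distribution.

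| Assumed correlation | Either direction, 5% each | Favouring montelukast, 5% each | Either direction, 2.5% each |
|---|---|---|---|
| 0 | 9.75% | 4.9% | 4.9% |
| 0.5 | 9.1% | 4.5% | 4.65% |
| 0.7 | 8.4% | 4.2% | 4.3% |
| 0.8 | 7.8% | 3.9% | 4.0% |
| 0.9 | 7.0% | 3.5% | 3.6% |

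**Step 3: effect of 2.5% each on intervals and power.**
On a normal approximation, interval width changes by 2.2414/1.9600 = 1.14. Power per endpoint stays at the 90.2% of Step 1, assuming d = 0.5 on each endpoint.

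**The case against.** **The analysis plan may settle the decision rule.** An article need not state whether one or both endpoints must succeed, and that omission alone would be no finding. If both must succeed, testing each at 5% causes no inflation. This stands, and it makes the error rates conditional. It does not remove the contradiction: {20a} fixes a level for all analyses, and that level disagrees with the one in {14}.

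**The reason for 2.5% is not stated.** Correct. Sample size {14} and {20a} both refer to the primary outcome in the singular, and neither links 2.5% to two endpoints. A Bonferroni split is the likely source, since 2.5% is 5% divided by two and there are two primaries, but it remains an inference.

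**The 7.0% to 9.75% range counts both directions.** It is a legitimate familywise rate. A reader might take it as the chance of wrongly claiming that montelukast works. The documents frame the hypothesis as improvement, so that chance is about half as large: 3.5% to 4.9%, against 2.5%.

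**A reader might also infer four primary tests.** Outcomes {12} says: "We will calculate both raw and norm-calculated standard scores". That sentence concerns cognitive data in general and only says that both scores are calculated. It does not make both scales primary, and the 8 points and SD of 16 in {14} belong to the standard-score scale. The documents do not support a four-test error rate.

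**Conclusion.** The contradiction is real. The planning level is two-sided 2.5%, as the arithmetic shows; the decision level is two-sided 5%, as the text states; and there are two primary endpoints. A primary p-value between 0.025 and 0.05 passes at one level and fails at the other, whatever the reason for the 2.5%.

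The size of the inflation rests on two assumptions: that success on either endpoint suffices, and that the correlation lies between 0 and 0.9. Under these, the two-sided familywise error is 9.75% down to 7.0%, and the chance of a false claim of benefit is 4.9% down to 3.5% against a nominal 2.5%. The sample size itself is sound for its stated level.

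**What to change.** Reconcile {14}, {20a} and the Processing speed section before the statisticians receive the allocation. Any one of these does so:

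1. **Keep both primaries, either sufficient.** In {20a}, test each at two-sided 2.5%, or use Holm or Hochberg at 5% overall, and report 97.5% intervals for the primaries. Keep p < .05 and 95% intervals for secondary outcomes. In {14}, say that 2.5% is two-sided and why.
2. **Name one primary endpoint** at two-sided 5%, make the other secondary, and restate {14} at that level.
3. **Require both to succeed** at two-sided 5%, and restate {14} with the power for the joint requirement.

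Option 1 is a change of wording: the sample stays at 200 and power per endpoint stays about 90%. Its cost is primary intervals about 14% wider. That figure is approximate, because the planned bias-corrected and accelerated intervals are not fixed multiples of a standard error. With Holm or Hochberg, a 97.5% interval can include zero when the stepwise test rejects, so the text should say which governs.

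Option 2 gives 94.2% power at 100 per arm. Under option 3, with d = 0.5 on both endpoints, joint power is at least 1 − 2 × (1 − 0.9424) = 88.5%, slightly below the stated 90% at that bound.

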#### Interim analyses {21b}

Interim analyses are not planned as unexpected serious adverse events related to the intervention are not expected. The trial participation for each patient is short, and they will be followed up in their local paediatric haematology centres.

#### Methods for additional analyses (e.g. subgroup analyses) {20b}

Analyses will consider how results differ according to age, whether the child had an SCI, oxygen content, overnight oxygen saturation, and sleep duration. Baseline demographics, age, sex, and most recent haemoglobin will be compared for those consenting to, and completing the trial and the non-consenters/non-completers to identify any potential biases and the generalisability of results.

Sensitivity analyses will also compare observations collected during higher UK COVID-19 restrictions versus lower/no COVID-19 restrictions. We will examine the impact of the COVID-19 pandemic on our trial outcomes by assessing the interaction between our treatment groups (montelukast versus placebo) and scores on the caregiver completed CEFIS in regression models. Finally, in addition to assessing hydroxyurea as a stratification factor, we will also determine if there is a hydroxyurea exposure × dose per kilogram effect on processing speed (e.g. does more prolonged hydroxyurea exposure after accounting for weight affect processing speed?)

#### Methods in analysis to handle protocol non-adherence and any statistical methods to handle missing data {20c}

All randomised participants will be included in analyses based on intention to treat. Missing data will be imputed under the assumption of the data being missing at random (MAR). Results will be compared with complete case analyses. The MAR assumption will be explored before the trial and before drop-outs occur. We will use multiple imputations for ITT analysis, but check the MAR assumption against reasons given for drop-out and complete case for per protocol to compare the results.

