#### Criteria for discontinuing or modifying allocated interventions {11b}

The CI and local PI in consultation with the respiratory physician (AG; author) may withdraw participants from the trial if they consider that the risk of continuing in the trial is too great, for example, if the child is experiencing side effects associated with montelukast or if they require montelukast to treat asthma symptoms. Each caregiver or legal guardian can choose to withdraw a participant from the trial at any time. If a caregiver or legal guardian expresses their wish to withdraw from the trial, the site research staff will first explain the importance of remaining in the trial. If they still wish to withdraw, the research staff will request that the collected data still be used. If a patient or guardian explicitly states they do not want to contribute further data to the trial, their decision will be respected. Research staff will record withdrawals and the patient’s reason on a case report form, and the local PI will note in the patient’s hospital records. If a participant chooses to discontinue their trial treatment, they will continue to be followed as closely as possible to the follow-up schedule defined in the protocol, providing they are willing. If the participant is withdrawn due to an adverse event, the CI will arrange for follow-up visits or telephone calls until the adverse event has resolved or stabilised. We will not replace participants who stop trial follow-up early. We do not anticipate any dose adjustments during the trial.

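### Children whom investigators withdraw from the trial are promised no week-12 test, and the planned checks of missing-at-random either cannot test it or cannot size a departure from it

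*Protocol article*

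**What the plan says.** Section {11b} of the protocol article describes two ways of coming off the allocated treatment.

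- **Investigator decision.** The CI and local PI, consulting the respiratory physician, "may withdraw participants from the trial if they consider that the risk of continuing in the trial is too great". The examples are "if the child is experiencing side effects associated with montelukast or if they require montelukast to treat asthma symptoms". For adverse-event withdrawals, "If the participant is withdrawn due to an adverse event, the CI will arrange for follow-up visits or telephone calls until the adverse event has" settled. No week-12 cognitive test is mentioned for these children.
- **Family decision.** "If a participant chooses to discontinue their trial treatment, they will continue to be followed as closely as possible to the follow-up schedule", provided they are willing.

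The same section adds: "Research staff will record withdrawals and the patient’s reason on a case report form", and "We will not replace participants who stop trial follow-up early".

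Section {20c} includes all randomised children by intention to treat and uses multiple imputation under MAR. It offers three checks on that assumption. One is a matter of timing: "The MAR assumption will be explored before the trial and before drop-outs occur". The other two come in one clause, which says the team will "check the MAR assumption against reasons given for drop-out and complete case for per protocol to compare the results".

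Section {20a} gives the primary model: the week-12 difference between arms, adjusted for hydroxyurea and for baseline as appropriate.

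**The concern.** The intention-to-treat claim needs week-12 scores from as many randomised children as possible. {11b} secures them when the family stops the drug. It does not secure them when the investigator withdraws the child, and that route is opened by side effects or by a need for the drug. Both triggers could be related to arm and to how the child is doing. {22} lists somnolence, headache and psychomotor hyperactivity among the frequent effects of montelukast, and secondary hypothesis (ii) expects fewer asthma symptoms on montelukast. Missing scores may therefore be informative.

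If they are, the primary estimate can be off while the planned comparison of imputed and complete-case results shows close agreement. That agreement would probably be reported as support for MAR, although it would appear either way.

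**Working it through.** **1. The plan's own figure.** Inputs from {14}: 100 per arm, difference 8, SD 16, 2.5% level (two-sided), power 90%.

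n per arm = 2 × (2.241 + 1.282)² × (16/8)² = 2 × 12.41 × 4 = 99.3, so 100. Power at 100 per arm is 0.902.

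The stated figure reproduces, with every child assumed to have an outcome. With 10% or 20% lost, power is 0.867 or 0.821.

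**2. Why imputation and complete cases agree.** Let X hold arm, hydroxyurea and baseline, with o for observed and m for missing rows. The complete-case fit is b = (Xo′Xo)⁻¹Xo′yo. Imputation from the same variables fills the gaps with Xm·b plus noise. Refitting gives, on average,

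(Xo′Xo + Xm′Xm)⁻¹ (Xo′Xo·b + Xm′Xm·b) = b.

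The true missing scores do not enter, so the comparison cannot respond to them.

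**3. Size of the bias.** Let p be the share withdrawn and δ the number of points by which withdrawn children fall below their MAR prediction, by arm (T montelukast, C placebo). Then

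bias = pT·δT − pC·δC.

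Unequal loss alone does no harm: with δ = 0 in both arms the bias is zero whatever the rates. If placebo withdrawals depart more, the sign reverses and the benefit is understated.

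**4. Simulation.** 1,500 trials per row, 100 per arm, SD 16, 20 imputations. The withdrawal rates, the departures, a baseline correlation of 0.6 and a completers' effect of 8 are assumptions; the documents give no rate, correlation or departure. With an effect of 8, δT = 8 means that withdrawn montelukast children lose the whole benefit (8 − 8 = 0). δT = 16 puts them 8 points below comparable placebo children and is an extreme case.

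| Withdrawn T / C | δT / δC | All children | Complete case | Imputed | Bias by formula |
|---|---|---|---|---|---|
| 10% / 10% | 0 / 0 | 8.02 | 8.05 | 8.05 | 0 |
| 5% / 5% | 8 / 0 | 7.65 | 8.06 | 8.06 | 0.05 × 8 = 0.4 |
| 10% / 5% | 8 / 0 | 7.25 | 8.05 | 8.06 | 0.10 × 8 = 0.8 |
| 10% / 5% | 8 / 8 | 7.55 | 7.98 | 7.99 | 0.8 − 0.4 = 0.4 |
| 20% / 10% | 8 / 0 | 6.42 | 8.07 | 8.07 | 0.20 × 8 = 1.6 |
| 20% / 10% | 16 / 0 | 4.87 | 8.06 | 8.06 | 0.20 × 16 = 3.2 |
| 10% / 10% | 8 / 8 | 7.95 | 7.97 | 7.97 | 0.8 − 0.8 = 0 |

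The imputed estimate minus the complete-case estimate averages between −0.004 and 0.008 points (SD 0.10 to 0.18) in every row, including the first, where MAR is true. The gap between the complete-case and all-children columns matches the formula.

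**5. The three checks side by side.** Exploring MAR before drop-outs has no missing data to work on. The complete-case comparison gives the same answer whether MAR holds or fails. Reasons by arm can raise suspicion, but they give no estimate of bias, and {20c} attaches no analysis to them. The completer comparison in {20b} uses baseline characteristics only.

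**The case against.** The strongest reply is that {20c} does not rely on the complete-case comparison alone. It names reasons for drop-out, {11b} has them recorded, and a listing by arm would show side effects or need for montelukast as causes of missing scores. This stands: a reader might infer that the plan has no means of noticing informative withdrawal, and the text does not support that. What it lacks is a means of judging the consequence.

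Second, the agreement in step 2 depends on the imputation model. Adherence and adverse-event data from the interim calls in Table 2, or the other of the two processing-speed endpoints, could enter as auxiliary variables and separate the two analyses. This also stands as a condition. No auxiliary variable is stated, and one would change the MAR assumption rather than test it.

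Third, differential withdrawal is not documented. {17a} blinds the CI, the local PIs and the data collectors, so suspected side effects can prompt withdrawal in either arm. A reader might conclude that side-effect withdrawals fall mainly on montelukast and asthma withdrawals mainly on placebo, and hence that the result will be biased. The documents make this plausible but do not show it.

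Fourth, {11b} does not say that testing is cancelled for withdrawn children. True; it simply promises them none, while it does promise scheduled follow-up to the other group.

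Fifth, the article condenses a fuller protocol and the analysis plan is not shown, so a tipping-point analysis may exist there. Its absence is not the point. The point is what {11b} and {20c} do state.

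**Conclusion.** Two things hold. {11b} lets children leave the trial for drug-related reasons without a promised week-12 test, which sits badly with the intention-to-treat analysis of all randomised children in {20c}. And of the three checks on MAR, one examines nothing, one agrees by construction if imputation uses the model's own variables, and one can flag a departure but not size it.

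The size is conditional. When only montelukast withdrawals depart from MAR, the bias is about the share withdrawn times the departure: 0.4 points at 5% and 8 points, up to 3.2 at 20% and 16 points, against the target of 8. It is about zero when rates and departures match across arms. All rates, departures and the correlation are assumptions, so no particular bias can be claimed for this trial.

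It is also tempting to read the per-protocol clause as equating complete cases with the per-protocol set. The wording is ambiguous: it may mean a complete-case analysis within that set. It needs clarifying and is not shown to be wrong. The plan should be changed on these points, since the remedy is cheap and concerns the primary outcome.

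**What to change.** **In {11b}:** leave the clinical decisions as they are, and reconcile the two routes with {20c} by separating the end of trial treatment from the end of data collection. Children taken off by the investigator keep the scheduled week-12 processing-speed test where the family agrees. The existing respect for families who want to give no further data stays.

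**In {20c}:**
- Delete the sentence on exploring MAR before drop-outs occur.
- Keep the complete-case analysis if wanted, but do not present its agreement with imputation as a test of MAR.
- Use delta-adjusted (tipping-point) imputation as the sensitivity analysis. Shift imputed scores separately by arm, guided by the recorded reasons, and report the shift at which the conclusion changes.
- State that the per-protocol set is defined by adherence and not by having complete data. A child who stopped the drug but attended week 12 has complete data without having taken treatment as planned.

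**Cost:** wording changes, a few week-12 assessments that are already in the schedule, and one extra sensitivity analysis.
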